### Data Processing and Statistics

All datasets will be analyzed using intention-to-treat. The findings from the ASAP questionnaire (Study Part A) will be descriptively reported and presented using appropriate measures such as mean ± standard deviation or median and interquartile range depending on distributions and scales of measurement. Additionally, the significance of variable associations (e.g., between physical activity levels and markers of well-being) will be examined using correlation and regression analyses.

To estimate the risk of non-response bias, wave analyses will be conducted according to Lewis et al. (26). Specifically, the responses of the first 10% percent of the participants (early responders) will be compared to those of the last 10% (late responders) by means of inferential statistics. The rationale behind this is that early responders are assumed to be more motivated than late responders which can be compared to non-responders. Hence, if the wave analyses do not provide significant findings, absence of non-response bias is concluded.

For study Parts B and C (randomized, controlled trial/controlled crossover trial), a prospective meta-experiment approach will be applied (27). For each country, the mean pre-post-differences between-groups including 95% confidence intervals (95% CI) will be calculated at the different time points. An a priori sample size calculation using an algorithm specifically designed to account for between-site variance in multi-center trials was performed (28). When achieving a sample size of *n* = 544 with an included drop-out rate of 20%, the trial will have 80.3% power to detect pre-post-differences with a minimal effect size (Cohen's *d*) of 0.25 at an alpha level of 0.05. To account for potential between-center variance, the data collected in each country will be pooled using a random-effects model (29). This leads to an aggregated effect size (weighted mean differences) demonstrating the overall effectiveness of the intervention while the different countries can still be compared by means of inspecting the 95% CI's. Heterogeneity between countries will be quantified by means of the *I*^2^ index (30). To further explore its potential sources (e.g., country, age, sex, baseline physical activity), a meta-regression with continuous and factorial independent variables will be performed (31).

Data analyses will be performed using standard statistical software packages (e.g., SPSS 22, SPSS Inc., Chicago, Illinois, USA and BiAs statistics, Goethe University, Frankfurt/Main, Germany). The significance level for all analyses will be set to α = 0.05.

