### Participants

The target population will include residents aged 18 and older from countries with (1) officially registered cases of the novel coronavirus (SARS-CoV-2) and (2) active governmental restrictions limiting public life via bans of public gatherings, forced restrictions of social, contact business closures, or lockouts. Recruitment will be performed by means of advertising in social media platforms (e.g., Youtube, Facebook, Twitter, Instagram) as well as health-related institutions (e.g., national chapters of the Exercise is Medicine initiative).

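### A non-significant comparison of early and late survey responders is taken as proof that non-response bias is absent (Part A)

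*Protocol article*

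**What the plan says.** The rule is in the protocol article under Data Processing and Statistics. The aim is given first, in cautious terms: "To estimate the risk of non-response bias, wave analyses will be conducted". The earliest tenth and the latest tenth of respondents are then compared "by means of inferential statistics". The stated rationale is that "early responders are assumed to be more motivated than late responders which can be compared to non-responders". The paragraph ends with a decision: "Hence, if the wave analyses do not provide significant findings, absence of non-response bias is concluded". The same section fixes the threshold: "The significance level for all analyses will be set to α = 0.05".

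No margin, smallest difference of interest, minimum wave size or power is attached to the rule, and no sample size is given for the survey. The only power statement in the article (544 participants, 80.3% power, d = 0.25) belongs to the randomised part. On how respondents are found, the Participants section says: "Recruitment will be performed by means of advertising in social media platforms". It adds health-related institutions as a second channel.

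**The concern.** The aim and the decision do not match. Estimating a risk calls for an estimate with its uncertainty. The rule instead gives a yes-or-no answer, and a p-value above 0.05 is read as yes, there is no bias. Failure to reject a null hypothesis is not evidence that the null is true. The rule also works backwards as a safeguard, because the fewer people answer, the more easily the survey passes.

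A second weakness lies in the inference itself. Both waves consist of people who answered. The step from late responders to non-responders is an assumption, and the test does not examine it. Even a precise finding that the two waves agree would say nothing about non-responders unless that assumption holds.

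At stake is the wording of the Part A results. The Introduction calls Part A a population-based survey, and its answers shape the Part B programme. A statement that non-response bias is absent would lend those results an assurance that the analysis cannot give.

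**Working it through.** The plan gives no figure of its own for this analysis, so there is nothing to reproduce. The check asks how the rule behaves over a range of survey sizes.

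**Inputs from the protocol article**
- Wave size: 10% of respondents each, so n = 0.10 × N per wave and 20% of the sample in total.
- Alpha: 0.05.

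**Assumptions**
- N (not stated): 500 to 10,000.
- Two-sided two-sample t-test on one item (the test is not named).
- True early-late difference d of 0.25 SD or 0.10 SD. The value 0.25 is borrowed from the minimal effect size for the randomised part; the article sets none for the survey.

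**Formulas**
- Power ≈ Φ(d × √(n/2) − 1.96). The table uses the exact t-test.
- Miss rate = 1 − power.
- Half-width of the 95% confidence interval in SD units = 1.96 × √(2/n).

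Example for N = 1,000, so n = 100: 0.25 × √50 = 1.77, and 1.77 − 1.96 = −0.19. This gives power of about 42% and a miss rate of about 58%. The half-width is 1.96 × √0.02 = 0.28 SD.

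| N | n per wave | Power, d = 0.25 | Miss rate, d = 0.25 | Power, d = 0.10 | 95% CI half-width (SD) |
|---|---|---|---|---|---|
| 500 | 50 | 23.6% | 76% | 7.9% | 0.39 |
| 1,000 | 100 | 42.1% | 58% | 10.8% | 0.28 |
| 2,000 | 200 | 70.3% | 30% | 16.9% | 0.20 |
| 5,000 | 500 | 97.7% | 2% | 35.2% | 0.12 |
| 10,000 | 1,000 | about 100% | about 0% | 60.8% | 0.09 |

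**Size needed for 80% power.** n = 2 × ((1.96 + 0.84)/d)². For d = 0.25 this is 252 per wave (N about 2,520). For d = 0.10 it is 1,570 per wave (N about 15,700).

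**What a pass means.** With N = 1,000 and an observed difference of exactly zero, the 95% confidence interval runs from −0.28 to +0.28 SD. It still contains 0.25 SD, yet the rule would record absence of bias.

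**Several items.** The article speaks of wave analyses in the plural, so the single-item miss rate is not the error rate of the whole rule. If five independent items each truly differed by 0.25 SD, the chance of missing all five would be 0.76⁵ ≈ 25% at N = 500 and 0.58⁵ ≈ 7% at N = 1,000. If only one item differs, or the items are strongly correlated, the figure moves back towards the single-item value.

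**The other direction.** If nothing truly differs, at least one of k independent items is significant with probability 1 − 0.95ᵏ: 23% for k = 5 and 40% for k = 10. At N = 10,000, a difference of only 0.10 SD is significant 61% of the time. The outcome of the rule therefore depends heavily on N and on the number of items, whatever the bias.

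**The case against.** The strongest reply is that comparing waves is a recognised check, that the article cites a source for it, and that Part A is descriptive. A multinational survey in seven languages could well exceed 2,520 respondents, which would give 80% power for 0.25 SD on a single item. All of this is fair, but it does not rescue the sentence. The comparison may stay; the conclusion drawn from it is what fails, and it fails even with high power.

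The reply does limit the point. A reader might infer more than the article supports:
- **That the test is underpowered.** No Part A sample size is given, so power is unstated and cannot be called low.
- **That the test is run country by country in small samples.** The rule refers to the participants as a whole. Analysis by country is described only for Parts B and C.
- **That early and late reflect staggered national launches or changing restrictions.** The article gives one 2-week survey period and no staggered dates.
- **That the plan declares the survey free of all selection bias.** The rule speaks of non-response bias only. People never reached by the advertising are a coverage question, which the check neither addresses nor claims to address.
- **That the randomised comparison is affected.** The rule has no bearing on the Part B or Part C effect estimates or on the trial's sample size.

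**Conclusion.** The point holds as a fault in a stated rule: a non-significant test of unstated power, on a fifth of the respondents and without a margin, is treated as proof of absence. The error is one of logic and does not depend on the survey size. Nothing elsewhere in the article withdraws the sentence.

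Its practical size does depend on N. The single-item chance of passing despite a true 0.25 SD difference falls from about 76% at 500 respondents to about 2% at 5,000, and is lower for the set if several items truly differ. These figures rest on assumed survey sizes, a two-sided t-test and one item. The point should be fixed. It is limited to the interpretation of the Part A survey.

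**What to change.** - Delete the sentence that concludes absence of non-response bias.
- Report the early-late standardised differences with 95% confidence intervals, as an indication of the risk of non-response bias. This matches the aim that the paragraph already states.
- State that a non-significant result does not exclude non-response bias, and that the check does not address people never reached by the open advertising.
- If a statement of no relevant difference is wanted, allow it only when the confidence interval lies wholly within a margin that the sponsor sets beforehand. The article gives no margin. For scale, suppose the 95% interval is used, the true difference is zero and an 80% chance of success is wanted. Then n = 2 × ((1.96 + 1.28)/margin)² per wave: 337 (N about 3,370) for 0.25 SD, 526 (N about 5,260) for 0.20 SD and 2,102 (N about 21,020) for 0.10 SD. These margins are illustrations, not recommendations.

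The cost is a change of wording and a few lines of analysis on data already collected. The price is a weaker permitted conclusion.

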#### Study Part B

Based on the results of study part A, the second part will consist of a multicenter, two-armed, randomized-controlled parallel group trial. Participants in the intervention group (IG), for a period of 4 weeks, will receive online workouts with video live-streaming using the appropriate software (e.g., Zoom, Zoom video communications, San Jose, California, USA; BlackBoard, Washington, DC, USA). Duration, frequency, and contents will be selected balancing (a) the needs of the population as indicated via the ASAP questionnaire and (b) scientific recommendations for exercise prescription. For example, the minimum training frequency will be once per week and minimum duration will be 10 min (21). To allow a higher degree of standardization between the countries, the instructors will be provided with modifiable demo workouts exhibiting different content-related focuses (e.g., strength, endurance, postural control/balance, cognition, relaxation), which can be individually adapted. The control group (CG) will not receive an intervention and is instructed to complete the outcome assessments (see below). Randomization (1:1 ratio) will be performed using a software algorithm of the online database used for survey delivery (Soscisurvey, Soscisurvey GmbH, Munich, Germany). To allow concealed group allocation, the participants will be automatically informed by the system about allocation upon survey completion at baseline.

A two-fold approach is used for recruitment. Firstly, upon completion of the ASAP questionnaire (study part A), each participant will be informed about the opportunity to participate in the subsequent intervention trials (Study Parts B and C). Second, the same recruitment strategies used for the initial survey (social media advertising and promotion via associations and societies) will be used to enhance recruitment.

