Some methodological considerations are needed. As home-exercise may become an important method to maintain PA during future confinements, it will be particularly interesting to study adherence. It has been reported that the feeling of being supported and the possibility to contacting the provider may facilitate compliance (47). As our exercises in study part A will be live-streamed and the participants can interact with the instructors, we believe this can improve training frequency compared to traditional home-exercise programs. Compliance will also be of importance in our CG. As it does not receive an intervention, participants may withdraw from the study. We chose two strategies to counteract this. Firstly, we offer them free database use in study Part B and thus, any participant enrolled will have a PA intervention. Secondly, the CG participants will be actively motivated to express their preferences regarding the video-database and, using their feedback, some workouts will be specifically tailored for them. Besides compliance, another issue relates to outcome assessment. We decided to use questionnaire assessments in both study parts, which is congruent with the objective to measure and improve subjective well-being and allows the achievement of large sample sizes. However, regarding PA assessments, it should also be noted that most persons tend to overestimate the own activity levels and that the recall of moderate-intensity activities is less precise than that of vigorous activities (48).

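### Estimating each country's effect from unadjusted pre-post change gives up precision that adjusting for the T1 value would recover at no cost

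*Protocol article*

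**What the plan says.** The Protocol article, Data Processing and Statistics, names the estimator for Parts B and C. For each country, "the mean pre-post-differences between-groups including 95% confidence intervals (95% CI) will be calculated at the different time points". The country results are pooled with a random-effects model into a weighted mean difference, and countries are compared by looking at their confidence intervals. The power statement refers to the same quantity: with a sample size of "544 with an included drop-out rate of 20" per cent, "the trial will have 80.3% power to detect pre-post-differences with a minimal effect size" (Cohen's d) "of 0.25 at an alpha level of 0.05".

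Neither a baseline covariate nor a longitudinal model is named for the effect estimate. Baseline physical activity appears once, as a possible source of heterogeneity in the meta-regression.

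The Outcomes section plans a baseline survey (T1) and weekly surveys T2 to T5 during the randomised part. Under Study Part B, participants learn their group only after completing the baseline survey. The T1 value is therefore a proper baseline covariate, and everyone randomised should have it.

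On the analysis set, the article says "All datasets will be analyzed using intention-to-treat". It gives no rule for missing surveys.

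**The concern.** A difference in mean change subtracts the whole baseline value, which fixes the baseline slope at 1. The data usually support a smaller slope. With equal variances the best slope is rho, which is below 1 for any questionnaire score measured weeks apart. Subtracting too much adds baseline noise to the estimate. It also carries part of any chance baseline imbalance into the result: a fraction 1 - rho of it, on average.

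What is at stake is the width of the intervals. The plan relies on country-level confidence intervals, both for comparing countries and as the input to pooling. Avoidable within-country variance makes those intervals wider than the collected data require and lowers the power of the pooled result.

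**Working it through.** **The plan's own figure.** Inputs from the article: 544 participants including 20% drop-out, d = 0.25, alpha 0.05, and 1:1 allocation ("Randomization (1:1 ratio) will be performed using a software algorithm"). Sidedness is not stated, so I assume two-sided. Power is approximately Phi(d / sqrt(2/n) - 1.96), with n per arm and d in SD units.
- All 544 evaluable (272 per arm): 0.25 / sqrt(2/272) = 2.916, power 83.0%.
- 544 x 0.8 = 435.2 evaluable (217.6 per arm): 0.25 / sqrt(2/217.6) = 2.608, power 74.1%.

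Neither equals 80.3%. The sample-size method is said to allow for between-site variance, and that input is not given. The figure can therefore be neither rebuilt nor shown to be wrong. This has no bearing on the present point.

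**Variance of the two estimators.** Let the outcome have SD s at baseline and at follow-up, with correlation rho. Variance per person:
- Change score: s^2 + s^2 - 2 rho s^2 = 2(1 - rho) s^2.
- ANCOVA on T1: (1 - rho^2) s^2 = (1 - rho)(1 + rho) s^2.
- Ratio: 2 / (1 + rho), above 1 for every rho below 1.

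With unequal SDs (sX at baseline, sY at follow-up), the change-score variance is sY^2 (1 - rho^2) + (sX - rho sY)^2. The second term is the excess and is never negative, so the direction does not depend on equal variances.

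**Size, with rho assumed.** Interval width scales with the square root of the variance ratio.

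| rho (assumed) | Change score | ANCOVA | Ratio | Variance saved | Interval wider by |
|---|---|---|---|---|---|
| 0.3 | 1.40 | 0.91 | 1.54 | 35% | sqrt(1.538) = 1.24, so 24% |
| 0.5 | 1.00 | 0.75 | 1.33 | 25% | sqrt(1.333) = 1.155, so about 15% |
| 0.7 | 0.60 | 0.51 | 1.18 | 15% | sqrt(1.176) = 1.085, so about 8% |
| 0.8 | 0.40 | 0.36 | 1.11 | 10% | sqrt(1.111) = 1.054, so 5% |

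Outside this range the ratio is 1.67 at rho 0.2 and 1.05 at rho 0.9.

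**Effect on power** (435 evaluable, two-sided, no between-site variance). The article does not say whether d uses the SD of change or of the score, so both are shown.
- d on the SD of change: 74.1% for the change score at any rho. ANCOVA gives 89.9% (rho 0.3), 85.3% (0.5), 80.7% (0.7) and 78.5% (0.8).
- d on the SD of the score, change score against ANCOVA: 59.6% and 78.0% (rho 0.3), 74.1% and 85.3% (0.5), 92.0% and 95.5% (0.7), 98.5% and 99.1% (0.8).

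**Repeated-measures alternative.** I compared a longitudinal model for T1 to T5 with a change score at T5 computed from observed pairs. Assumptions: compound symmetry, and 5% of participants lost before each of T2, T3, T4 and T5. The change score has 1.56, 1.37, 1.22 and 1.16 times the variance of the model at rho 0.3, 0.5, 0.7 and 0.8. ANCOVA at T5 is only 1% to 4% less efficient than the model (ratios 1.014 to 1.044). Nearly all the gain comes from baseline adjustment.

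**Pooled estimate.** With k countries of equal within-country variance v and between-country variance tau^2, the random-effects variance is (v + tau^2)/k. Adjustment lowers v, so the pooled estimate gets the full saving only if tau^2 is zero, and less otherwise.

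**The case against.** **The wording does not exclude adjustment.** Regressing the change on group and baseline gives exactly the ANCOVA treatment effect, and covariates are often left to a fuller plan that is not shown. This stands as a caution. The natural reading is still an unadjusted difference in mean change, because baseline is mentioned only in the meta-regression. That regression explores why countries differ; it does not adjust the effect within a country.

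**The plan is coherent and unbiased as it stands.** The sample size and the estimator refer to the same quantity, and under randomisation with complete data a difference in mean change estimates the right effect. Chance imbalance is already reflected in its interval. All of this stands, and it limits the point to precision.

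**The gain may be small.** At high rho it is. If d is on the SD of the score and rho is 0.7 or more, power is already 92% or higher and rises little. In a very small country with high rho, the cost of estimating a slope could cancel the gain. The number and size of countries are not stated, so this cannot be settled from the documents.

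**Stronger readings that a reader might infer.** The first is that the plan is a completer analysis that contradicts intention-to-treat, since a change needs two values and the Discussion says of the control group: "As it does not receive an intervention, participants may withdraw from the study". The documents do not show this. The second value may be observed or imputed, the article gives no missing-data rule either way, and such a rule is commonly left to the full plan. The Discussion also sets out two measures to retain controls. Nor would a repeated-measures model settle the matter, because it too may leave out people with no survey after T1. Any figure for bias from control-arm withdrawal would need drop-out rates by arm and outcomes of leavers, which the documents do not give. The second reading is that a change score ignores the baseline correlation. It does not: its variance, 2(1 - rho) s^2, depends on rho. It fixes the slope at 1 instead of estimating it.

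**Conclusion.** The point holds as one of precision. As written, the country-level estimator has 2/(1+rho) times the variance of a baseline-adjusted one, that is 1.54 at rho 0.3, 1.33 at 0.5 and 1.11 at 0.8. Adjustment would remove about 35% to 10% of the within-country variance. These sizes rest on an assumed rho, equal variances at baseline and follow-up, and samples large enough that estimating one slope costs little. The direction, a loss unless the best slope happens to equal 1, needs only the last of these. The comparison is with ANCOVA at a single time point; a repeated-measures model gives slightly larger figures under the further assumptions shown. No bias, no breach of intention-to-treat and no error in the stated power follows from this. It is a free improvement.

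**What to change.** State in the analysis section that each country's treatment difference is estimated with the T1 value of the same outcome as a covariate. Either of two forms will do:
- ANCOVA at each time point, with group and T1 value as terms; or
- a repeated-measures model on T2 to T5 with treatment-by-time and baseline-by-time terms. This also uses the T2 to T4 data of people who miss T5.

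Then pool the adjusted country differences with the random-effects model already planned. Weighted mean differences, I-squared and the meta-regression can stay as they are.

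The cost is a change of wording and a little programming. No new data, assessments or participants are needed, and the sample size need not change.

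### The printed sample size, drop-out allowance and 80.3% power do not fit together: on the plain reading, 544 with 20% loss gives about 74%

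*Protocol article*

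**What the plan says.** All the figures stand in the Protocol article, Data Processing and Statistics. The sample size sentence plans n = 544 and says that "with an included drop-out rate of 20%, the trial will have 80.3% power to detect pre-post-differences with a minimal effect size", given as a Cohen's d "of 0.25 at an alpha level of 0.05". The calculation is said to come from an algorithm that allows for between-site variance, but neither the number of sites nor the variance entered is printed. Allocation is 1:1 (Procedures and Interventions, Study Part B).

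For the analysis, the section says that "the mean pre-post-differences between-groups including 95% confidence intervals (95% CI) will be calculated at the different time points", country by country, and that "the data collected in each country will be pooled using a random-effects model". It closes with: "The significance level for all analyses will be set to α = 0.05". Whether tests are one-sided or two-sided is not stated.

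**The concern.** A sample size that already contains a 20% drop-out allowance should deliver its stated power on the 80% who remain. Here it does not, under the ordinary two-group calculation. An allowance for between-country variation in the effect would call for more participants still.

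What is at stake is how a null result is read. If the pooled estimate is not significant, a reader will take the trial as having had 80% power against d = 0.25. On the plain reading the type II error is about 26% (100 − 74), not 19.7% (100 − 80.3). The allowance is not a formality either: the Discussion expects that control participants, who receive no programme during the randomised phase, may leave the study.

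**Working it through.** **Inputs**
- N = 544, drop-out 20%: 544 × 0.8 = 435.2 analysed, or 217.6 per arm at 1:1.
- d = 0.25, alpha = 0.05, claimed power 80.3%.
- Two-sided testing is an assumption, made because inference rests on 95% confidence intervals. One-sided is also tried.
- d is taken on the SD of the analysed pre-post difference (assumption).
- The number of countries K and the between-country SD of the effect tau (in units of d) are not printed. They are set to zero effect first, then varied.

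**Formula.** SE = √(4/N + tau²/K); power = Φ(d/SE − z), with z = 1.960 two-sided or 1.645 one-sided. The exact t-test gives results up to 0.2 points lower, shown in brackets.

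**Step 1: try to reproduce 80.3% (tau = 0)**
- 435.2 analysed, two-sided: SE = √(4/435.2) = 0.0959; 0.25/0.0959 − 1.960 = 0.648; power 74.1% (74.0%).
- 544 analysed, two-sided: SE = √(4/544) = 0.0857; 0.25/0.0857 − 1.960 = 0.955; power 83.0% (82.9%).
- Drop-out handled as 544/1.2 = 453.3 analysed, two-sided: 75.8% (75.7%).
- 435.2 analysed, one-sided: 2.608 − 1.645 = 0.963; power 83.2% (83.1%).

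None of these comes within two points of 80.3%.

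**Step 2: number needed for 80.3%, two-sided**
- Per arm: 2 × (1.960 + 0.852)² / 0.25² = 253.1, so 254, or 508 analysed in total.
- Randomised at 20% loss: 508/0.8 = 635. The incorrect multiplication 508 × 1.2 gives 610. Neither is 544.
- With 544 randomised, the tolerable loss is 1 − 508/544 = 6.6%.

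**Step 3: detectable effect with 435.2 analysed**
- At 80% power: (1.960 + 0.842) × 0.0959 = 0.269. At 80.3%: 0.270.

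**Step 4: add between-country variance in the effect**
- For 80.3% power, SE² must equal (0.25/2.812)² = 0.00790.
- With 544 analysed, 4/N = 0.00735, which leaves tau²/K = 0.00055. That is tau = 0.052 with 5 countries or 0.088 with 14. For example, tau = 0.05 over 5 countries gives 80.5%. So 80.3% is reachable if no one is deducted.
- With 435.2 analysed, 4/N = 0.00919, already above 0.00790. Under this model no value of tau gives 80.3%. Assuming tau of 0.05 to 0.10 over 7 to 12 countries, power is about 68% to 73%.

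**Step 5: what would restore 80.3% with 435.2 analysed, two-sided**
- The residual variance would have to fall to 0.00790/0.00919 = 0.86 of the value assumed, a reduction of about 14%.
- If d is on the total SD and the comparison is made within country, this is a site ICC of about 0.14.
- If d is on the raw-score SD, the variance of the change is 2(1 − r) times the raw variance; 2(1 − r) = 0.86 gives a pre-post correlation r of about 0.57.

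**The case against.** The strongest reply is that a simple t-test is not the calculation that was done. The planned estimate is formed within each country and then pooled, so between-country differences in outcome level drop out. If the algorithm standardised d on the total SD, a site ICC of about 0.14 would bring 435 analysed back to 80.3%. The sample size sentence also names the contrast but not the SD behind d; on the raw-score SD, a correlation of about 0.57 would do the same. A one-sided test gives 83.1% with 435, and a tau of about 0.06 (5 countries) to 0.11 (14 countries) would then bring it to 80.3%. The source is also a condensed article, so the site inputs may stand in the full protocol.

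Most of this stands as a limit on the claim. A reader might infer that true power is at most 74%, or type II error at least 26%. The document does not support either as a bound, because these inputs are unseen. A reader might also infer that the investigators certainly forgot the drop-out. Step 4 makes that plausible but does not prove it.

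The reply does not remove the point. N, drop-out, d, alpha and power are all printed, and they disagree on their plain reading. Each rescue needs an input that the text does not state. Change scores already remove stable country-level differences, so an ICC of 0.14 for them cannot be taken for granted. A one-sided calculation would not match the 95% confidence intervals. And if 544 is the analysed number, the drop-out is not included in it.

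**Conclusion.** The point holds as an inconsistency among printed figures, not as proof of the trial's true power. With 544 randomised 1:1, 20% lost, two-sided 5%, d = 0.25 on the SD of the analysed difference and no between-country effect variance, power is about 74%, some 6 points below the stated 80.3%. The detectable effect at 80% power is about 0.27, not 0.25. The lower figures with between-country variance (about 68% to 73%) depend on assumed values of tau and K and illustrate direction only.

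The closest two-sided match to 80.3% under the plain standardisation is all 544 analysed with a small effect variance. In that case the power could be right and the drop-out statement wrong. The article does not allow a choice between these explanations, so the remedy has to cover both.

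**What to change.** Re-run the calculation with about 435 analysed, two-sided 0.05 and the site inputs actually used, and restate the power. Say in the same sentence whether 544 is randomised or analysed, which SD d refers to, and how many countries and what between-country variance were entered. Then:

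- If those inputs do support 80.3% with about 435 analysed, print them and keep the figure.
- If they do not, write: *544 randomised, about 435 analysed after 20% drop-out, about 74% power for d = 0.25 (two-sided 0.05) before between-country effect variance; detectable d about 0.27 at 80% power.*
- If 544 was the analysed number, say so and correct the drop-out phrase; the randomised number is then 544/0.8 = 680.

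The cost is one sentence, and a stated power that may become less favourable. If the sample stays at 544 randomised, no further recruitment is needed to make the statement correct. Keeping 80.3% on the plain reading would need about 635 randomised.
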